**Descriptive variables**					
Age, gender, country of origin, educational level, employment, and civil status.	Self-reported questions	X			
Living conditions and housing standards		X	X	X	X
Cognitive status	Montreal Cognitive Assessment, MOCA [49,50].	X			
Functional limitations	Housing Enabler [48].	X	X	X	X
Environmental barriers	Housing Enabler [48].	X			

List of abbreviations: *ADL* Activities of Daily Living, *EQ-5D* European Quality of Life-5 Dimensions, *HA* Housing Adaptation.

#### Primary outcomes

Usability denotes the effectiveness of, efficiency of, and client satisfaction with a specific environment or technical device. It focuses on the performance of tasks and activities and the related perception of satisfaction [39]. Usability is also central in current Swedish building legislation; thus, it is an important outcome of an HA. It is measured with a revised version of UIMH [28,29]. The client assesses his or her satisfaction with the housing design in activity performance. The instrument comprises 18 items that reflect 18 different personal, instrumental, leisure, and work-related activities.ADL dependence and difficulty is an operationalization of independence and is thus related to the legislative framework for HA and measured with the ADL Staircase [26,40]. It comprises nine items on feeding, transfer, using the toilet, dressing, bathing, cooking, transportation, shopping, and cleaning. For items on which the participant is rated as independent, he or she is also asked to state whether the corresponding activity is performed with or without difficulty [41].

#### Secondary outcomes

Client levelFear of falling is measured using the short form of the Falls Efficacy Scale-International [42], which consists of seven items (i.e., activities).Falls are targeted based on previous research [43] and measured using structured questions that concern frequency, fall rate, locations, injuries [44], and the frequency of near falls [45].Participation and satisfaction are assessed by means of study-specific questions based on previous research [46] and on the current goals of HA. This includes responding to 8 statements concerning the frequency of and client satisfaction with performance-related participation and togetherness-related participation.Health-related quality of life is measured by means of the EQ-5D-5 L [47]. This is a standardized instrument consisting of a descriptive system targeting mobility, self-care, usual activities, pain/discomfort, and anxiety/depression, in combination with the EQ visual analogue scale.Data on the type of MD and the frequency and location of its use are collected by means of the personal component of the Housing Enabler (HE) instrument [48], as well through questions used in previous research [43].Client goal fulfillment is investigated by means of open questions concerning specific goals and achievements with the HA before and after the intervention to the client and occupational therapist.

Societal levelHealth-economic data are important for societal planning purposes and in this study are collected in the following direct-cost categories: time spent by the OT with each client (both preparation time and direct contact); time other professionals spend with each client; time spent training the OT at the intervention site and other direct costs for training; time and other costs for travel; the cost of other consumables used for each client; the amount of the grant given to each client; and time for the assistance provided by formal and by informal (family) caregivers. Data is collected from an ad hoc resource-use questionnaire compiled by the OTs, by during the follow-up period retrieving grant applications, certificates, invoices and formal grant decisions, related to each case from the municipality office, and by using client-reported data on assistance received by informal caregivers. Data from the EQ-5D-5L instrument can be used for cost-effectiveness calculations, as well.Client relocation data are targeted by using a single dichotomous item question. This outcome is included because relocation to another ordinary or sheltered housing facility is sometimes an alternative to HA or a solution when HA proves insufficient.

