## Background

The global prevalence of moderate and severe disabilities is estimated at 15% of the general population and at 50% among those aged 60 and up [1]. To a large extent, disabled persons experience problems in daily life owing to physical and social barriers in the environment [1]; therefore, disability can be reduced by adapting the environment [2].

In Sweden, in compliance with the Housing Adaptation Act [3], housing adaptations (HAs) can be provided to people who experience a declining functional capacity to eliminate physical environmental barriers in the home in order to promote independence and safety. HA in this study are defined according to the Swedish law as adaptation of solid features in the home [3], such as removal of thresholds, installation of grab bars or removal of a bath tub and installation of a shower. HA is a publicly funded intervention, administered by a given municipality in response to a client’s application. The full costs of the HA are granted based on needs assessment and certification by a health professional, most often an occupational therapist (OT) employed by the municipality.

When it comes to outcomes of HA, previous research has indicated that HAs improve independence in terms of activity and participation [4–7], reduce difficulty performing activities [8], and improve the usability of the home [4,5]. In this respect, then, the aims of the intervention seem to have been fulfilled. Moreover, falls and the consequences thereof are common, often resulting in injuries, morbidity, and increased health-care costs [9], but research has shown that fall-related disability is positively affected by HA, particularly among people who have a history of falling [6,10]. Thus, it seems that HAs have the potential to counteract injuries in the home and contribute to increased independence.

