### Hypothesis and aims

The hypothesis of this study is that a new intervention strategy for OTs that takes a research-based and structured approach to assessing and evaluating clients who request new HAs can increase the usability of the home; maintain or increase activity, participation, and health-related quality of life, as well as MD use; and decrease fall incidences and the fear of falling (with respect to the standard approach in ordinary practice). An additional hypothesis is that the new intervention strategy will yield health-economic benefits.

The primary aim of this paper is to describe the design of a project evaluating the effects of using a research-based strategy for managing housing adaptations (HAs). The evaluation targets clients’ perspectives in terms of activity, participation, usability, fear of falling, fall incidence, use of mobility devices, and health-related quality of life, and determines the societal effects of HAs in terms of costs. Additional aims of the project are to explore and describe this strategy in relation to experiences and expectations (a) among clients and cohabitants and (b) occupational therapists in ordinary practice.

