#### Effects on the societal level

Cost, cost-effectiveness, and cost-utility analyses will be performed from the perspective of the municipalities. The analysis of costs will consider the following direct-cost categories in both the experimental and the control groups.

In order to estimate more correctly the resources used in the process of HA, the assistance provided by informal caregivers will also be assessed and considered in the cost analysis. The value assigned to an hour of informal caregivers’ assistance will be equal to the hourly salary of an unskilled care assistant.

The cost-effectiveness analysis will compare the costs and outcomes of the two trial arms. As outcomes measures we will use the ADL dependency change over the trial period and the number of institutionalizations and housing relocations. Because both the costs and the effects of the interventions will occur over a period of one year, it will not be necessary to adjust for the time delay or to discount the measures.

Three incremental cost-effectiveness ratios (ICER) will be calculated by taking the difference in costs divided by the difference in the three outcome benefits between the two groups: one unit of ADL score gain, one institutionalization avoided, one relocation avoided. All available data on client and societal levels will be used to identify the variables included in the analysis in order to answer the hypotheses. The ICER will represent the additional costs of gaining, through the intervention, an additional unit of these outcomes measures.

In a later step, probabilistic sensitivity analyses (PSA) will also be performed on the three models using the software TreeAge Pro 2009. Results from the PSA will be presented as an acceptability curve, graphically illustrating the probability that the intervention is cost-effective over a range of willingness-to-pay values.

A cost-utility analysis (CUA) will estimate the ratio between the cost of an intervention and the benefit it yields in terms of quality-adjusted life years. The PSA of this model will follow a procedure similar to that of the cost-effectiveness analysis.

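### The cost aim is societal but the analysis takes the municipal view, and health-care savings from avoided fall injuries have no stated route into the cost numerator

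*Protocol article*

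**What the plan says.** **Aim and hypotheses.** The Abstract and Hypothesis and aims say that the evaluation "determines the societal effects of HAs in terms of costs". Hypothesis and aims expects the strategy to "decrease fall incidences and the fear of falling" and adds that "the new intervention strategy will yield health-economic benefits".

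**Rationale.** The Background describes falls and their consequences as "often resulting in injuries, morbidity, and increased health-care costs".

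**What is costed.** In Secondary outcomes, under the label Societal level, health-economic data "are important for societal planning purposes and in this study are collected in the following direct-cost categories". The list holds OT time, "time other professionals spend with each client", OT training, travel, consumables, the grant, and hours of formal and family care. The sources are a resource-use form completed by the OTs, municipal case documents, and clients' reports of informal care. The cost row of Table 1 names staff, material, travel and administration and then ends in an open etc.

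**Perspective.** Effects on the societal level opens by saying that the cost, cost-effectiveness and cost-utility "analyses will be performed from the perspective of the municipalities". It then also values informal caregivers' hours, at the wage of an unskilled care assistant.

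**Falls.** Falls are a secondary outcome, "measured using structured questions that concern frequency, fall rate, locations, injuries". No sentence links them to a cost.

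**The concern.** The aim and two section labels are societal, while the declared perspective is municipal. The perspective is also not purely municipal, because family care is a cost that falls outside the municipality. So the analysis goes beyond the municipal view for one item and leaves out the item that the protocol's own rationale names, namely the health-care cost of falls.

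If the falls hypothesis is true, the strategy is charged for OT time, training and travel but not credited with treatment avoided elsewhere. A reader who takes the stated aim at its word would read a municipal-plus-family result as a societal one. The primary outcomes are unaffected. At stake is the answer to the economic aim and hypothesis.

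**Working it through.** The protocol gives no figure to reproduce. The check sets the sections side by side, then writes down what is missing from the ratios.

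**1. Is there a route for health-care cost?**

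| Place | Content | Health-care use named? |
|---|---|---|
| Secondary outcomes, cost list | OT time, other professionals' time, training, travel, consumables, grant, formal and informal care | No hospital, emergency, primary-care, rehabilitation or drug item |
| Secondary outcomes, sources | OT form, municipal documents, client report of informal care | No health-care register or use question |
| Table 1, cost row | Staff, material, travel, administration, etc. | Not named |
| Effects on the societal level | Announces cost categories, but no list follows; adds informal care | Not named |

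**2. Form of the ratios.** Let ΔC be the incremental cost over the listed categories, ΔE the incremental effect, and H = (fall injuries avoided) × (health-care cost per injury).

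- As planned: ΔC / ΔE, with ΔE in turn an ADL unit, an institutionalization avoided, a relocation avoided, and a QALY.
- With fall-related health care included: (ΔC − H) / ΔE.

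The same H is missing from all four numerators. If falls decrease, ΔC is overstated by H against a societal view. If they increase, it is understated.

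**3. What still gets in.** Extra care after an injury is costed through formal and informal care time. Table 1 marks that item at T1 and T4 only, so a temporary rise in between can be missed. Injuries can also act on ADL, institutionalization and QALYs. Those are effects, and they do not stand in for treatment cost avoided.

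**4. Size, on assumptions only.** The documents give no injury rate and no unit cost. Assume that 5 to 15% of clients a year have a fall injury needing care, at EUR 3,000 to 8,000 each, with 20% fewer under the strategy:

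- low: 0.05 × 0.20 × 3,000 = EUR 30 per client
- high: 0.15 × 0.20 × 8,000 = EUR 240 per client

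**5. Precision at the midpoints.** Take 10% against 8%, EUR 5,500 per injury, and 117 completers per arm (117 is the protocol's required number per municipality).

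- Saving: 0.02 × 5,500 = EUR 110 per client
- Injured clients: 0.10 × 117 ≈ 12 against 0.08 × 117 ≈ 9
- Standard error from injury counts alone: 5,500 × √(0.10 × 0.90/117 + 0.08 × 0.92/117) ≈ EUR 206

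The standard error is nearly twice the saving.

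**6. Can the collected data support a scenario?** Table 1 asks about falls over the last six months. T3 then covers months 0 to 6 after the adaptation and T4 covers months 6 to 12, without overlap. T2, at 3 months, reaches back before the adaptation and overlaps T3. This assumes that the injury questions share the six-month recall.

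**The case against.** The strongest defence is that leaving out health-care cost fits the perspective declared. The documents do not say who pays for treating a fall, so nothing shows that it belongs in a municipal numerator. That stands, and it is why the municipal base case need not be abandoned. It does not reconcile that base case with a societal aim, and the inclusion of family care shows that the municipal boundary is not kept.

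A second defence is that the list may be incomplete. Other professionals are not defined, the Table 1 row is open-ended, the analysis section announces categories that do not follow, and it says that all available client and societal data will be used to choose variables. An article also condenses. These points rule out a claim that health-care staff time is certainly absent. None of them names treatment of fall injuries or a source for it, and the conflict between aim and perspective is in the printed text.

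Two stronger readings are tempting:

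- *Savings from avoided falls cannot enter any economic result.* The documents do not support this. Care time is in the numerator, and ADL, institutionalization and QALYs are in the denominators.
- *The omission could reverse the sign of the incremental cost.* One could set EUR 30 to 240 against the four visits (90 + 3 × 45 = 225 minutes, or 3.75 h; EUR 94 to 150 at an assumed EUR 25 to 40 per hour). But the visits are one gross component. Preparation, the 5-day course, travel, grants and care time are left out, and the control site's own OT time is not subtracted. The comparison says nothing about the sign.

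**Conclusion.** The point holds in limited form. The stated aim is societal, the analysis is municipal plus informal care, and the health-care saving that the rationale relies on has no stated route into the numerator of any of the four ratios. Under the falls hypothesis, the direction is an incremental cost that is too high for a societal reading. The size cannot be derived from the documents. EUR 30 to 240 per client rests wholly on the assumed injury rate, unit cost and 20% reduction, and only illustrates a possible order of magnitude. The conclusion rests on the text and does not depend on that range. It should be corrected because it concerns a declared aim and hypothesis, but it does not touch the primary outcomes.

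**What to change.** 1. In Effects on the societal level, state the base-case perspective as municipal plus informal care. Calling it municipal alone would be wrong while family hours are valued.
2. In the Abstract and in Hypothesis and aims, limit the cost conclusion to that perspective.
3. Add one societal scenario. Value the fall injuries reported at T3 and T4 (months 0 to 12) with the same external unit cost in both arms, varied over a stated range. Cost per injury, or per injury type if the questions record type; the article says only that they concern injuries. Confine the unit cost to health care, so that care time already in the base case is not counted twice.
4. Report the three ICERs and the cost-utility ratio with and without the scenario.

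**Cost.** A few sentences and one extra analysis, using the fall-injury answers already planned. The drawbacks are self-reported injuries, few events and so an imprecise scenario, and unit costs from outside the trial. The scenario adds only fall-related health care, and its label should say so.

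### Institutionalizations avoided are an effect in the cost-effectiveness ratios, but no residential care cost is listed, so the cost difference is distorted whenever institutionalization differs between the arms

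*Protocol article*

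**What the plan says.** Under Effects on the societal level, the protocol article states: "Cost, cost-effectiveness, and cost-utility analyses will be performed from the perspective of the municipalities". On effects it says: "As outcomes measures we will use the ADL dependency change over the trial period and the number of institutionalizations and housing relocations". The three ratios are expressed per "one unit of ADL score gain, one institutionalization avoided, one relocation avoided", and a cost-utility analysis is added. Informal care is valued at the hourly pay of an unskilled care assistant.

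The cost items are listed under Secondary outcomes, at the societal level, as "direct-cost categories". They are occupational therapist time, "time other professionals spend with each client", training, travel, consumables, the adaptation grant, and care time, worded as "time for the assistance provided by formal and by informal (family) caregivers". The named data sources are a resource-use questionnaire filled in by the therapists, the municipality's paperwork on the adaptation grant, and client report of informal help. Effects on the societal level also announces a list of cost categories, but none follows there, so the list under Secondary outcomes is the only one.

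Table 1 records formal and informal care as self-reported weekly minutes, marked at T1 and T4 only. Its cost row names staff, material, travel and administration and is then left open. Relocation is one yes/no item that covers moves to ordinary and to sheltered housing alike. Table 1 has no separate row for institutionalization.

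**The concern.** One event enters the two halves of the ratio on different terms. In the denominator, a move to an institution is a bad outcome to be avoided. In the numerator, care given at home is charged, including informal care, but nothing on the list represents the lodging or facility cost that takes over when the client moves.

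People in sheltered housing are excluded at entry (Participants), so every institutional stay arises during follow-up, which is the period being costed. An arm that keeps more clients at home is charged for their home care and is not fully credited with the residential cost it avoids. An arm with more moves is not fully charged for them. The article hypothesizes a health-economic benefit of the strategy, and this cost difference feeds every ratio that would be used to judge it.

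**Working it through.** The plan gives no unit cost, institutionalization rate or ICER, so there is no stated figure to reproduce. The check is algebraic.

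**Notation, per client over the one-year horizon**
- D: incremental programme cost of the intervention
- pC, pI: institutionalization risk in the control and intervention arms
- R: residential cost of one institutionalized client, for the share the municipality bears
- f: share of R that the listed items capture, in practice through formal-care minutes (0 to 1)
- h: care cost of the same client if kept at home

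**Cost difference as the plan would compute it**

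ΔC(f) = D + (pI − pC)(f·R − h)

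**ICER per institutionalization avoided, for pC > pI**

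ICER(f) = ΔC(f)/(pC − pI) = D/(pC − pI) − f·R + h

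With residential cost fully counted, f = 1. The error is therefore ICER(f) − ICER(1) = (1 − f)·R. It does not depend on D, h or the difference between the arms.

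**Illustration.** All values are assumed, on an index where R = 100: D = 5, h = 40, pC = 10%, pI = 5%.
- f = 0: (5 + 0.05 × 40)/0.05 = 7/0.05 = 140
- f = 0.4: 5/0.05 = 100
- f = 0.7: (5 − 0.05 × 30)/0.05 = 3.5/0.05 = 70
- f = 1: (5 − 0.05 × 60)/0.05 = 2/0.05 = 40

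With D = 2 the sign changes: (2 + 2)/0.05 = +80 at f = 0, and (2 − 3)/0.05 = −20 at f = 1. A cost-saving intervention would then appear to cost money.

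**Reverse direction.** Take pC = 5%, pI = 10% and D = 5. ΔC is 5 − 0.05 × 40 = 3 at f = 0 and 5 + 0.05 × 60 = 8 at f = 1. The omission now makes the intervention look cheaper than it is.

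**Other ratios.** The error in ΔC is (pC − pI)(1 − f)·R whatever the denominator. The ADL, relocation and quality-adjusted life-year ratios all use this ΔC, so each is affected unless pC = pI or f = 1.

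**When a client who moves looks cheaper than one at home.** This needs f·R < h. In the illustration that means f < 0.4, or f < 0.2 if h = 20.

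**How large f could be.** The caregiver-time item is not limited to care at home, so residential staff time could be reported under it. Three features make full capture doubtful. It is self-reported weekly minutes. It is marked only at T1 and T4, which gives no duration for a move in between. And the therapists' assessment before certification (The intervention) concerns help needed in the home. Minutes of care cannot carry lodging or facility cost, so f = 1 is not plausible.

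**The case against.** The strongest reply is that the omission is not proven to be total. Formal-caregiver time and other professionals' time carry no restriction to the home, so some residential staff cost may be recorded. This stands. A reader might infer that institutional care is free in this analysis, and that a client who moves always looks cheaper. The documents do not support that: it holds only if f·R < h. Nor do they say that a client who moves is recorded with zero minutes. Such a client might be interviewed in the new setting, be missing, or count as a drop-out.

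Second, the list may not be closed. Table 1's cost row is open-ended, the analysis section says all available data will be used to choose variables, and a condensed article may leave valuation to a fuller plan. This stands only in part. The article itemizes both the costs and their sources, and no named source would yield a residential cost.

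Third, the payer share is not stated. This also stands, and the size of the bias depends on it. It does not make the question irrelevant, because the plan itself counts institutionalizations avoided as a benefit in a municipal analysis.

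Fourth, adding the cost might seem to count the event twice, once as cost and once as effect. But the numerator already takes the home-care consequence of a move and omits only the residential one. In the ADL and quality-adjusted life-year ratios, institutionalization is not the denominator at all.

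**Conclusion.** The point holds in a limited form. The plan counts institutionalizations avoided but lists no residential or sheltered-housing cost, so residential cost is understated. The error in the ICER per institutionalization avoided is exactly (1 − f)·R if the intervention reduces institutionalizations. If it increases them, the intervention is flattered. The other ratios inherit the error in the cost difference.

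Two stronger readings should be resisted. One is that the bias necessarily runs against the intervention: its direction depends on which arm has more moves, and the documents do not give that. The other is a percentage size. A reader might assume a day rate and compare the result with the mean adaptation cost implied by the Background (EUR 115.5 million / 76,000 ≈ EUR 1,520). The documents give no day rate, length of stay or difference in institutionalization. That mean is also a poor yardstick, because both arms receive adaptations and the relevant comparator is the incremental cost between arms. The size cannot be computed from the documents. The index figures above show only the mechanism and the possibility of a sign change.

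The conclusion rests on two assumptions: that the municipality bears some share of residential care, and that formal-care minutes do not capture all of it.

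**What to change.** Make three changes.
1. Add to the cost list under Secondary outcomes a category for days in sheltered or institutional housing during follow-up, multiplied by the municipality's own day rate, for the share the municipality bears. State that share and vary it over a range in the sensitivity analysis.
2. With the relocation item, record the date of the move and its type: ordinary housing, or sheltered or institutional housing. The single yes/no item supplies neither, and the count for "the number of institutionalizations and housing relocations" needs the type as well.
3. Exclude institutional staff minutes from the formal-care item for those days, so that they are not counted twice.

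Dropping the ratio per institutionalization avoided would not be enough, because the same cost difference feeds the cost-utility analysis and the other two ratios.

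The cost is two extra data items per client who moves, one unit price per municipality, and a small amount of costing work.

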#### Sample size calculation

The power calculation is based on data from a longitudinal study of the HA process [4,5]. Current power estimates are calculated based on primary outcomes: (1) dependence in daily activities, measured by means of the Activities of Daily Living (ADL) Staircase [26] revised version [27]; and (2) usability in the home, measured by the Usability in My Home (UIMH) instrument [28,29].

According to formal calculation, a sample size of 117 people in each municipality is required in order to detect the effect of the intervention with a statistical power equal to 80%. This size is based on an expected improvement of 0.5 in the ADL Staircase score and one of 1.5 on the UIMH score. This calculation is based on the assumption that an HA is effective in both experimental and control municipalities but that the effect is greater at an experimental site.

Given that we expect a drop-out rate of 30% over time in both groups owing to frailty, a total of 170 participants will be recruited at both experimental sites and the same number at the control site. Based on data from previous research, we anticipate that approximately 50% of those will use MDs outdoors or indoors [4,5], thus allowing meaningful sub-group analyses.

For the explorative segment targeting users’ perspectives, 20 clients and 10 cohabitants will be strategically selected for qualitative interviews. The selection will be based on data collection at T1, and the ambition is to make the sample as diverse as possible [30] in terms of sex, age, and MD use. Ideally, 10 in 20 clients should be living alone, whereas the remaining 10 should be cohabiting. The 10 significant others of cohabiting clients will also be invited for individual interviews.

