**Secondary outcome**					
Fear of falling	The Short Falls Efficacy Scale-International [42].	X	X	X	X
Fall incidence	Retrospective self-report on falls incidences during the last six months	X	X	X	X
Mobility devices	Self-reported use and need	X	X	X	X
Participation and satisfaction	Self-reported aspects of participation and satisfaction.	X	X	X	X
Health-related quality of life and quality adjusted life years (QUALYs)	EQ-5D-5L [47].	X	X	X	X
Cost	Item on costs for staff, material, travel, administration, etc.	X	X	X	X
Repeated HA	Self-reported question and register data from the municipality		X	X	X
Relocation	Self-reported question		X	X	X
Formal and informal care	Items on formal and informal care, who, and minutes per week, self-reported	X			X

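### The plan fixes a cost-effectiveness ratio per institutionalization avoided, but the only stated measure is one self-reported yes/no relocation item that does not record where the client moved

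*Protocol article*

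**What the plan says.** The section Effects on the societal level names the outcomes for the cost-effectiveness analysis: "As outcomes measures we will use the ADL dependency change over the trial period and the number of institutionalizations and housing relocations". It then fixes three ICERs, each with its own denominator: "one unit of ADL score gain, one institutionalization avoided, one relocation avoided". A probabilistic sensitivity analysis is planned for each of the three.

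The section Secondary outcomes (societal level) describes the measure: "Client relocation data are targeted by using a single dichotomous item question". The reason given for including it is that "relocation to another ordinary or sheltered housing facility is sometimes an alternative to HA", so both kinds of move come under the one item.

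Table 1 is presented as the overview of all outcome measures and other data. Its relocation row gives the source as "Self-reported question" at 3, 6 and 12 months (T2 to T4). It has no row for institutionalization. For the neighbouring outcome, repeated housing adaptation, the source is "Self-reported question and register data from the municipality".

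On attrition, Sample size calculation states that "we expect a drop-out rate of 30% over time in both groups owing to frailty".

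**The concern.** An ICER is a cost difference divided by an effect difference, so each of the three needs its own measured denominator. Two of them are counts of moves, one a specific kind of move and the other moves in general. The only stated instrument returns yes or no. A yes does not say whether the client went to another ordinary dwelling, to sheltered housing or to an institution.

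At stake is one of three pre-stated cost-effectiveness results, together with its acceptability curve. A later analysis plan cannot reliably recover a destination that nobody wrote down.

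A second issue concerns who answers. The item is self-reported at follow-up visits, and drop-out is expected because of frailty. Frailty may also lead to a move into care. Moves after a client has left follow-up are outside the item's reach.

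**Working it through.** **1. Denominators against data sources**

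| ICER denominator | Stated measure | Result |
|---|---|---|
| ADL score gain | ADL Staircase, T1 to T4 | Measured |
| Institutionalization avoided | None in Table 1 or the outcome sections | No stated source |
| Relocation avoided | One yes/no item, self-report, T2 to T4 | Countable as any move only |

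**2. What the yes/no item leaves open.** The documents give no event counts, so suppose 12 clients answer yes in the control group and 8 in the intervention group (assumed figures).

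- Relocations avoided: 12 − 8 = 4.
- Institutionalizations lie between 0 and 12 in the control group and between 0 and 8 in the intervention group.
- Institutionalizations avoided therefore lie between 0 − 8 = −8 and 12 − 0 = +12.

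The item alone does not fix even the sign of that denominator. Any institutional move that is counted also sits inside the relocation count, so the two ICERs overlap unless the plan separates them.

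**3. Drop-out: the plan's own figures.** Inputs from Sample size calculation are 117 evaluable, 30% drop-out and 170 recruited, read here as 170 per group.

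- 117 / (1 − 0.30) = 167.1, rounded up to 168. The stated 170 agrees, allowing for rounding.
- Lost by 12 months: 170 × 0.30 = 51 per group. Remaining: 170 − 51 = 119.

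**4. What drop-out could do to the ICER.** Let s be the share of all events that occurs among drop-outs and goes unrecorded. Assume s is equal in both groups, the risk is computed among the 119, and the cost difference is unchanged.

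- Observed risk difference = true difference × (1 − s) / 0.70.
- ICER multiplier = 0.70 / (1 − s).

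| s (assumed) | Multiplier |
|---|---|
| 0% | 0.70 / 1.00 = 0.7 |
| 30% (proportional share) | 0.70 / 0.70 = 1.0 |
| 50% | 0.70 / 0.50 = 1.4 |
| 80% | 0.70 / 0.20 = 3.5 |

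Under these assumptions the multiplier does not depend on the event rate itself. It passes through 1 at s = 30%, so the direction of bias turns on a quantity that the documents do not give.

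**5. Worst-case bounds.** Take the same assumed 12 and 8 observed events, with 51 of 170 unknown in each group. The difference, control minus intervention, runs from (12 − 8 − 51) / 170 = −27.6 percentage points to (12 + 51 − 8) / 170 = +32.4 percentage points. These are extremes, not expectations.

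**The case against.** The strongest reply is that other data could fill the gap. Table 1 collects living conditions and housing standards at all four time points, and formal and informal care at T1 and T4. Follow-up is by home visit, so staff would normally see the dwelling. Drop-out data are collected. The ICER section also says that all available client-level and societal-level data will be drawn on to choose the analysis variables. In a condensed article, the wording of questionnaires may sit elsewhere.

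Part of this stands. These are possible sources, so it would be too strong to say that the yes/no item is the only place where a destination could appear. But no passage ties any of them to institutionalization. Drop-out data are assigned to process evaluation. The article does not merely leave the measure out: it states a one-item measure and states an analysis that needs more than that item gives.

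Four stronger readings are tempting, and the documents do not support them.

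- **Both move-based ICERs are impossible.** A yes/no item is enough to count any move, so the relocation ICER can be produced.
- **Clients who drop out never report a move.** The item is asked at three visits and drop-out accrues over time, so some will have reported a move before leaving.
- **Drop-out inflates the ICER by 1.4 to 3.5 fold.** Those figures require drop-outs to hold 50% to 80% of events. At 30% there is no bias, and below that it reverses. The calculation also holds the cost numerator fixed, although informal-care time is client-reported and would be lost as well.
- **Capture differs by arm.** Different staff follow clients at the experimental and control sites, but the item is self-reported and the protocol says identical outcome data are collected everywhere. A difference is conceivable but not shown.

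**Conclusion.** The concern holds in limited form. As written, the plan leaves one of its three ICERs, the one per institutionalization avoided, without a stated data source. The relocation ICER is computable only as any move and would overlap it. This follows from setting the sections side by side and needs no assumption.

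The yes/no item does not capture moves after a client leaves follow-up, with 51 of 170 per group expected to be lost by 12 months. Whether this biases the ICER, and in which direction, cannot be settled from the documents. The multipliers of 0.7 to 3.5 only show how the answer varies over assumed shares of 0% to 80%.

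The usability and ADL Staircase outcomes, the ADL-based ICER and the cost-utility analysis do not use this item. The point still deserves correction while data are being collected, because the destination of a move could not be recovered reliably afterwards.

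**What to change.** 1. Replace the yes/no item with the date and destination of any move: ordinary housing, sheltered housing or institution.
2. State which destinations count as institutionalization, including whether sheltered housing does, and whether the two ICER outcomes overlap.
3. Record the same item, plus death, in the drop-out data already collected.
4. Use municipal records as a supplement where consent and access allow. The retrieval already planned covers housing-adaptation grant papers. The register data listed for repeated adaptations are not shown to cover residence or death, so a further source may be needed.
5. If destination cannot be recorded, drop the institutionalization ICER and report a single any-relocation ICER.

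The cost is one extra response field per follow-up visit and on the drop-out record, and possibly a consent addition for record follow-up. Tracing every withdrawn client through records would cost more, which is why records are proposed only as a supplement.
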